In neurological rehabilitation, the use of MI has generally been associated with physical practice (PP). Motor imagery has several advantages, such as the opportunity to increase the number of repetitions safely and autonomously, without excessive fatigue, in addition to allowing the mental training of motor tasks, when and where the patient wants or is able to perform them. Furthermore, MI enables more demanding or complex motor tasks, such as gait, or when PP is impossible or very difficult. Despite these advantages, MI is a complex process that is not easy to integrate into clinical practice [15]. Its association with PP, however, seems to be more effective than PP alone in enhancing motor function [16].

Two studies that associated MI with PP, in order to determine the motor effects on individuals with PD, showed a significant decline in bradykinesis [17] and an improvement in the kinematic aspects of gait [18]. Another study that correlated MI with PP showed no gait improvement in individuals with PD [19]. A fourth study that compared MI with relaxation sessions, both associated with PP, found no improvement in the mobility of these patients [20]. The protocols used, different training times between studies and the lack of follow-up precluded confirming the duration of the effects observed.

In light of the gaps in the methodologies presented, a therapeutic plan can be devised involving MI, which has been shown to be promising, albeit still inconclusive. As such, there is a need to develop more effective training protocols in order to optimize the rehabilitation process of individuals with PD. To that end, a new MI protocol associated with gait was created for patients with PD, based on the protocols of El-Whishy [18] and Santiago [19], but differing in terms of training time, observation method and follow-up.

Few PD studies have investigated EEG functions during gait activity. Therefore, this study aims to contribute to the literature on the pattern of brain activation (coherence intra- and inter-hemispheres and the spectral power of alpha and beta rhythms) of individuals with PD during gait activity, before and after the MI intervention. Clinical quantitative measures of gait and mobility, most commonly investigated by other studies, will also be analyzed and correlated with EEG data.

Thus, this randomized clinical trial protocol should determine the effects of MI training on the gait and EEG activity of individuals with PD.

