From the ninth training session onwards, EG subjects will carry out both MI and PP of gait with two tasks. Mental imagery will involve a supermarket, where the patient will be instructed to imagine walking around the environment, shopping for products beginning with a letter that will be drawn at each series.

The dual task performed in stage 5 will be different at each session, progressing in difficulty. In the ninth session, the patient must say words starting with the letters drawn in each series; in the 10th session, they will be asked the names of fruits according to the letters selected; in the 11th session, it will be the names of animals and, finally, in the 12th session they will perform subtractions, starting with a decreasing sequence of 90 minus 3. Furthermore, another motor activity will be associated with gait such as picking up an object along the way and bringing it back to the start of the course. In the CG, subjects will only engage in dual-task gait, following the same protocol of activities established for the EG.

This protocol will be applied on the day following initial assessment, executed in 12 training sessions of at most 90 min, three times a week for 4 weeks. Experimental group individuals will be instructed to continue to practice MI of gait in their daily lives during the training period. They will be instructed to fill in a diary with information on the quantity of days, number of repetitions and duration of the training performed at home. All the participants will be reassessed 1, 7 and 30 days after the last training session in terms of the kinematic variables of gait using the Qualisys Motion Capture System®, mobility using the TUG and EEG activity via Emotiv EPOC+. During the gait test, the patient will be instructed to walk as they did over the past days, since the beginning of the study participation. As the evaluator is blind to allocation groups, they will not know whether the patient is making corrections or not in the gait. The schematic study design is shown in Fig. 2.

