### Data analysis

Data analysis will be conducted with the following variables: (1) Kinematic: speed (m/s), stride length (m), stance and swing time (s) of the most affected limb, hip range of motion, maximum hip extension during stance (°), maximum hip flexion during swing (°), maximum knee flexion during swing (°) and ankle dorsiflexion (°); (2) EEG activity: alpha (8–12 Hz)- and beta (13–30 Hz)-frequency bands; and (3) Mobility: average time to conduct the TUG.

Analysis of variance with repeated measures will be used to determine whether there are statistically significant differences between baseline, post training and monitoring measures of the CG and the EG.

Group descriptions will be presented as means and standard deviations. Intention-to-treat analysis will be conducted for dropout data, using the last available value to represent the absent assessment sessions.

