## Discussion

The protocol aims to determine the effects of motor-imagery training on gait and the EEG activity of individuals with PD. This protocol was based on those of Santiago [19] and El-Whishy [18], but the type of observation, follow-up and training time were altered.

In Santiago’s protocol [19], the action was visualized using images of the sequential stages of gait. It is a static method that does not resemble the real pattern. The protocol, based on El-Whishy [18], involves observing the action using videos of normal gait and of a patient with PD, enabling better identification of gait changes and familiarizing individuals with their daily gait pattern, making the training more dynamic.

The second alteration is related to the lack of follow-up in El-Whishy’s protocol [18]. It is known that the presence of a follow-up is important in confirming the retention time of the observed effects. This protocol, which is different from the aforementioned, suggests a follow-up in order for these effects can be assessed.

The third and last alteration is related to the training used. Based on the study by Santiago [19] and El-Whishy’s protocol [18], it is suggested that patients with PD require more time to achieve favorable results. As such, this study proposed to use a longer training period in order to investigate whether the increase in MI training associated with PP is able to produce benefits superior to those of PP alone.

The methodological strength of the proposed protocol lies in the fact that it is a prospectively registered randomized controlled study. The study also includes random allocation and masking, in addition to an intent-to-treat analysis. The sample size was calculated to provide an adequate statistical base to identify intergroup differences in the primary outcome. This study has limitations, given that the participants and therapist cannot be blinded in complex interventions. Moreover, it is difficult to ensure that patients will imagine movement, that they will use this imagination in the kinesthetic modality and in the number of repetitions proposed.

In conclusion, the results of the present study may provide an important advance in neurological rehabilitation. An easy-access, low-cost intervention may help improve gait, EEG activity and mobility in individuals with PD.

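### Carrying the last value forward assumes, for every participant with a missing visit, the answer to the retention question that the follow-up is meant to settle

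*Protocol article*

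**What the plan says.** The Data analysis section gives the test and the missing-data rule in two separate sentences.

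- Test: "Analysis of variance with repeated measures will be used to determine whether there are statistically significant differences between baseline, post training and monitoring measures" in the two groups.
- Missing data: dropouts are kept in under the label of intention to treat, "using the last available value to represent the absent assessment sessions".

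The article names no second method and no sensitivity analysis. The assessment times are in the section on PP of gait: "All the participants will be reassessed 1, 7 and 30 days after the last training session".

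The purpose of these visits appears twice. The Background says of earlier studies that "the lack of follow-up precluded confirming the duration of the effects observed", among other shortcomings. The Discussion lists follow-up as one of three changes from the source protocols, because "the presence of a follow-up is important in confirming the retention time of the observed effects".

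**The concern.** LOCF makes a different assumption depending on when a participant stops attending.

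- **Seen at day 1 or 7, absent at day 30:** the earlier value stands in for day 30. No decay is assumed.
- **Lost during training:** the baseline value stands in for all three post-training visits. No effect is assumed.

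Neither assumption comes from data, and each bears on what the trial wants to learn at day 30. Some decay is plausible. Training has ended by then, and the experimental group is only "instructed to continue to practice MI of gait in their daily lives during the training period". For participants with imputed values, the analysis therefore presupposes how long the effect lasts. The rule applies to the primary outcome, hip range of motion, as well as to the secondary outcomes.

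**Working it through.** **Inputs from the article (Sample size estimates).** SD 7.2°; power 80%; 95% confidence, read as two-sided alpha 0.05; 17 per group; 10% allowance for losses; final sample 20 per group.

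**Inputs that the article does not give.** The between-group difference D just after training, the share r of it truly retained at day 30, the share m missing day 30, and the share q of the missing who have a post-training value. All four are assumptions below. The 10% allowance is the only guide to m.

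**The plan's own figure.** The 34 cannot be reproduced, because one mean (54.7°) is given and no difference. Solving backwards from 17 per group:

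D = 7.2 × (1.960 + 0.842) × √(2/17) = 6.92°, or 0.96 SD.

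This serves only as a scale for illustration. On losses, 34 × 1.10 = 37.4 and 34 / 0.90 = 37.8, so both rules round up to 38. The stated 40 leaves room for 6 losses, or 6/40 = 15%.

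**Bias formula.** Take equal missingness in both arms, unrelated to outcome, and a carried post-training value that shows the full D.

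- Expected 30-day difference under LOCF = (1 − m) × r × D + m × q × D
- True 30-day difference = r × D
- Bias = m × D × (q − r)

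**Results with D = 6.92°.**

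| Missing at day 30 | q = 1, r = 0.5 | q = 1, r = 0 | q = 0, r = 0.5 |
|---|---|---|---|
| 10% | +0.35° | +0.69° | −0.35° |
| 15% | +0.52° | +1.04° | −0.52° |
| 20% | +0.69° | +1.38° | −0.69° |

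In the q = 1, r = 0.5 column, apparent retention is 55%, 57.5% and 60% instead of 50%. If day-7 values are carried and part of the effect has already gone by day 7, the positive biases shrink.

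**Simulation check.** Settings: 20 per arm, SD 7.2°, assumed correlation 0.7 between visits, 4,000 runs per scenario, t-test on change from baseline to day 30, with q = 1 and r = 0.

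| Missing | LOCF difference | LOCF rejection rate | Observed-only difference | Observed-only rejection rate |
|---|---|---|---|---|
| 10% | 0.68° | 5.8% | −0.02° | 5.3% |
| 15% | 1.04° | 7.4% | 0.00° | 5.3% |
| 20% | 1.38° | 9.7% | 0.01° | 5.2% |

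These runs fix the number missing per arm. If that number varies at random, the LOCF rejection rates are 6.4%, 8.3% and 11.0% (20,000 runs each).

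**Unequal dropout.** Suppose, purely for illustration, that both arms gain 6.9° from physical practice, with no difference between them, and that 20% of the experimental group and 5% of the control group are affected. The shift is 6.9 × (0.20 − 0.05) = 1.04°. It goes against the experimental group if these participants leave during training. It favours the experimental group if they miss only day 30 and the gain has by then decayed to zero.

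**The case against.** Four points can be made for the plan.

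1. **The effect is limited.** A reader might infer that LOCF builds full retention into the 30-day result. It does not. Only imputed participants with a post-training value are given full retention, and the estimate moves in proportion to the share missing. At 10% missing the shift is at most a tenth of the post-training effect. At day 1 only baseline can be carried. This stands.

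2. **The sign is open.** A reader might infer that LOCF always favours a lasting effect. The bias is positive only when q exceeds r. Losses during training pull the other way, and the article gives neither quantity. This stands. A bias whose direction cannot be known in advance is still a reason not to rely on the rule.

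3. **No false precision was found.** A reader might infer that filled-in values make the ANOVA error term too small. Repeated-measures ANOVA was simulated with no group difference, equal missingness of 10–20%, 20 per arm and correlation 0.7. The group × visit test rejected in 4.7–5.3% of runs under LOCF, against 4.8–5.2% with complete data (6,000 runs per scenario). The concern is bias, not the error term.

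4. **The inputs are not documented.** D is back-solved, and using it as a within-arm gain has no basis in the article. Only the experimental group has the imagery stage, home practice and a diary, so unequal dropout is possible. But both arms share the 90-minute ceiling, and no differential loss is reported. The sizes above are therefore illustrations.

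None of this supports LOCF as the sole method in a trial that adds follow-up in order to measure retention.

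**Conclusion.** The point holds in a limited form. The only stated missing-data rule assigns no decay to participants who miss day 30 after an earlier post-training visit, and no effect to those lost during training. With all missing participants having a post-training value and D of about 6.9°, the 30-day difference is overstated by about 0.35° (half retained) to 0.7° (none retained) at the planned 10% loss, and by 0.7° to 1.4° at an assumed 20%. Against an SD of 7.2°, 0.35° is about 0.05 SD and 1.4° about 0.19 SD. With a different mix of early and late losses the bias can vanish or reverse. The sizes rest on assumed D, r, m and q; the nature of the two assumptions does not. This is a should-fix: modest in size at the planned loss, aimed at a declared purpose of the trial, and cheap to remove.

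**What to change.** Replace both the repeated-measures ANOVA sentence and the LOCF sentence in Data analysis. Changing only the second would leave two conflicting methods. Suggested text:

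> All randomised participants are analysed in their allocated group with a likelihood-based linear mixed model. Baseline and the 1-, 7- and 30-day values are all modelled as responses, with visit and group × visit effects, a common baseline mean in the two groups, an unstructured covariance matrix and Kenward-Roger degrees of freedom. Missing visits are not imputed; the analysis assumes that data are missing at random. LOCF, if reported, is a labelled sensitivity analysis.

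Modelling baseline as a response matters. A model restricted to participants with a post-training value would drop those lost during training and weaken the intention-to-treat claim in the Discussion.

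Cost: no new data and slightly more analysis work. The day-30 interval may be wider, and the result rests on missing at random, which cannot be tested from the observed data. The change should be recorded before the group codes are broken.

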## Discussion

The protocol aims to determine the effects of motor-imagery training on gait and the EEG activity of individuals with PD. This protocol was based on those of Santiago [19] and El-Whishy [18], but the type of observation, follow-up and training time were altered.

In Santiago’s protocol [19], the action was visualized using images of the sequential stages of gait. It is a static method that does not resemble the real pattern. The protocol, based on El-Whishy [18], involves observing the action using videos of normal gait and of a patient with PD, enabling better identification of gait changes and familiarizing individuals with their daily gait pattern, making the training more dynamic.

The second alteration is related to the lack of follow-up in El-Whishy’s protocol [18]. It is known that the presence of a follow-up is important in confirming the retention time of the observed effects. This protocol, which is different from the aforementioned, suggests a follow-up in order for these effects can be assessed.

The third and last alteration is related to the training used. Based on the study by Santiago [19] and El-Whishy’s protocol [18], it is suggested that patients with PD require more time to achieve favorable results. As such, this study proposed to use a longer training period in order to investigate whether the increase in MI training associated with PP is able to produce benefits superior to those of PP alone.

The methodological strength of the proposed protocol lies in the fact that it is a prospectively registered randomized controlled study. The study also includes random allocation and masking, in addition to an intent-to-treat analysis. The sample size was calculated to provide an adequate statistical base to identify intergroup differences in the primary outcome. This study has limitations, given that the participants and therapist cannot be blinded in complex interventions. Moreover, it is difficult to ensure that patients will imagine movement, that they will use this imagination in the kinesthetic modality and in the number of repetitions proposed.

In conclusion, the results of the present study may provide an important advance in neurological rehabilitation. An easy-access, low-cost intervention may help improve gait, EEG activity and mobility in individuals with PD.

## Data Availability

Not applicable.

## Abbreviations

CG: Control group
CNPq: National Council for Scientific and Technological Development
EEG: Electroencephalographic
EG: Experimental group
LIAM: Laboratory of Intervention and Analysis of Movement
MI: Motor imagery
MIQ-R: Revised Movement Imagery Questionnaire
MMSE: Mini-Mental State Examination
PD: Parkinson’s disease
PP: Physical practice
TUG: Timed Up and Go Test
UFRN: Federal University of Rio Grande do Norte
